### Sample size calculation

The G*power software (version 3.1) was utilized to determine the minimal sample size necessary to identify a significant between-group difference in the present research. A systematic review and meta-analysis indicated that the pain and function are the primary outcome (32) with an effect size of 0.25 for CMS in detecting changes or improvements in pain and function scores in patients with FS (33). Based on a prior two-way repeated analysis of variance (ANOVA) F test, with a power of 0.80, an effect size of 0.25, three groups, six measurements, correlation among repeated measures of 0.5, and an alpha level of 0.05, 93 participants were required for this study. To account for a conservative drop-out rate of 20%, the final sample size will therefore be 39 participants in each group, for a total of 117 participants.

### Selection of subjects

#### Inclusion criteria

Patients aged ≥18 years old with unilateral shoulder pain.A minimun 25% reduction in the ROM in at least two planes compared to the unaffected shoulder (34).Patients with a duration of pain ≤ 9 months and a visual analogue scale (VAS) for shoulder pain ≥ 3.Normal shoulder X-rays.

#### Exclusion criteria

Patients with secondary FS and additional shoulder conditions (e.g., shoulder joint deformity, fractures, dislocations, arthritis, cervical radiculopathy, and previous shoulder surgery, rotator cuff injuries or subacromial impingement syndrome, calcified tendinitis, and osteoarthritis).Other shoulder pain secondary to conditions such as fibromyalgia, rheumatic diseases, and trauma.Patients who received an intra-articular corticosteroid injection in the affected side within the preceding 3 months.Patients diagnosed with bilateral FS.Other comorbidities (i.e., cardiovascular, neurological, hepatic or renal disorders, malignant tumors, high fever, infectious diseases and cognitive impairments, etc).Individuals unable to finish the MRI scan.Patients with cognitive dysfunction, mental illness or inability to understand and cooperate with the investigators or provide informed consent.

### Setting and recruitment

A total of 117 individuals who comply with the inclusion criteria will be recruited from Seventh People’s Hospital of Shanghai University of Traditional Chinese Medicine and neighboring communities using flyers, posters, and referrals from an orthopaedician, physical therapist or occupational therapist. The participants will be invited to undergo an in-person examination and evaluation to guarantee that they satisfy the inclusion criteria. In addition, we will inform all participants of the study’s purpose, methodology, prospective benefits and the principle of voluntary participation. Recruitment began on 1 September 2025 and will continue until 117 individuals are enrolled.

### Randomization, allocation concealment and blinding

Each eligible participant will be associated with a randomly generated numerical code generated by SPSS software (IBM Corp. Released 2013. IBM SPSS Statistics for Windows, Version 29.0. Armonk, NY: IBM Corp.). To minimize any potential bias, participants will be randomly allocated to 3 groups according to pain intensity: mild pain (VAS 3–4), moderate pain (VAS 5–6), and severe pain (VAS 7–10) as variables (35, 36). Participants form each group will be randomly divided into groups A, B and C; thereafter, all groups A, B and C will be consolidated to create new groups (intervention group A, intervention group B and control group C) to minimize the bias of the results. The outcomes of the participants grouping will be sealed in opaque envelopes by an independent researcher and disclosed only at the time of allocation. Furthermore, therapists with equivalent qualifications, responsible for administering rTMS, NMES, and conventional rehabilitation programs, will likewise adhere to randomization and be randomly allocated to one of the groups. The visibility of the rTMS intervention prevents the operators from being blinded to the allocation of the intervention. Consequently, blinding will be implemented for both patients and assessors, as well as statisticians responsible for data collection and final statistical analysis in this study, to avoid any potential implementation and measurement bias.

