### Intervention methods

The intervention will be administered at the rehabilitation medical center of the Seventh People’s Hospital of Shanghai University of Traditional Chinese Medicine. All participants will receive the conventional rehabilitation program (CRP) recommended by the FS rehabilitation guidelines (37), which will include low-high grade joint mobilization, stretching exercise, passive and active limb movements, muscle strengthening, and self ROM exercises like different directions reaching, grasping and daily actions that are motivational and appropriate for the participants. Based on the CRP (30 min), control group C will receive Sham rTMS (20 min) + NMES (20 min); Intervention group A will receive LF-rTMS (20 min) + NMES (20 min); and Intervention group B will receive HF-rTMS (20 min) + NMES (20 min). The intervention for the three groups will be provided for 20 sessions (5 sessions per week, 4 weeks), each lasting 70 min.

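### Therapists are allocated to one arm each, so between-therapist variance enters the arm comparison, while the planned test and the sample size treat patients as independent

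*Protocol article*

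**What the plan says.** Under Randomization, allocation concealment and blinding, the protocol article states that therapists of equal qualification, "responsible for administering rTMS, NMES, and conventional rehabilitation programs, will likewise adhere to randomization and be randomly allocated to one of the groups". The same section says of masking that "The visibility of the rTMS intervention prevents the operators from being blinded to the allocation of the intervention", and that "blinding will be implemented for both patients and assessors, as well as statisticians responsible for data collection and final statistical analysis".

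Under Intervention methods, every participant also receives a conventional programme of "low-high grade joint mobilization, stretching exercise, passive and active limb movements, muscle strengthening, and self ROM exercises". It takes 30 minutes of each session, and the course is "20 sessions (5 sessions per week, 4 weeks), each lasting 70 min".

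The Abstract and Data analysis sections plan a two-way repeated-measures ANOVA with effects of group, time and their interaction. Sample size calculation gives 93 participants, raised to 117 (39 per arm) for 20% drop-out. Neither the analysis nor the sample size has a therapist component. The number of therapists is not given. The limitations paragraph of the Discussion mentions that the operator cannot be blinded, but not that therapists belong to single arms.

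**The concern.** The conventional programme is meant to be the same background in all three arms. Under the stated rule, different people deliver it in each arm. It is largely hands-on care, and it acts on pain, daily activities, range of motion and strength, which are the four components of the primary outcome, the Constant-Murley Score. If therapists differ in effect, patients of the same therapist resemble each other, and that shared part does not average out across arms because no therapist works in more than one.

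The observed difference between two arms is then the treatment difference plus a difference between two small sets of therapists. The planned test estimates its error only from variation between patients, so it can declare an rTMS effect that is partly or wholly a therapist effect. The protocol presents the allocation of therapists as part of its protection against bias, but the nesting is what creates this variance component.

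**Working it through.** **1. The plan's own figure.** Inputs from Sample size calculation: f = 0.25, three groups, m = 6 measurements, ρ = 0.5, α = 0.05, power 0.80. For the between-groups F test,

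λ = f²·N·m / [1 + (m − 1)ρ], with df = (2, N − 3).

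At N = 93: λ = 0.0625 × 93 × 6 / 3.5 = 9.96, and power is 0.8001. Drop-out: 93 / 0.80 = 116.25, rounded up to 117, or 39 per arm. The stated size reproduces exactly. It is the size for the between-group main effect with independent patients, which is the contrast that carries the therapist effect. (The within-between interaction with the same inputs would need only 24.)

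**2. Assumptions.** The document gives neither the number of therapists per arm (t) nor the ICC. The ranges used are t = 1 to 6 and ICC = 0.01 to 0.10, with n = 93 / 3 = 31 analysed per arm. The work is on the scale of the patient's mean score, with total variance 1.

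**3. One therapist per arm, exact.** With no treatment effect, the between-arm mean square has expectation 1 + (n − 1)·ICC and the within-arm mean square 1 − ICC. Their ratio is

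R = [1 + 30·ICC] / (1 − ICC).

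The 5% critical value of F(2, 90) is 3.10, so the true type I error is P(F(2, 90) > 3.10 / R).

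| ICC | R | Type I error |
|---|---|---|
| 0.01 | 1.30 / 0.99 = 1.31 | 0.100 |
| 0.02 | 1.60 / 0.98 = 1.63 | 0.156 |
| 0.05 | 2.50 / 0.95 = 2.63 | 0.313 |
| 0.10 | 4.00 / 0.90 = 4.44 | 0.501 |

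**4. Several therapists per arm, simulation** (20,000 runs per cell; ordinary F test that ignores therapist):

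| Therapists per arm | ICC 0.01 | 0.02 | 0.05 | 0.10 |
|---|---|---|---|---|
| 1 | 0.101 | 0.159 | 0.314 | 0.503 |
| 2 | 0.074 | 0.098 | 0.183 | 0.301 |
| 3 | 0.067 | 0.078 | 0.132 | 0.217 |
| 4 | 0.063 | 0.072 | 0.112 | 0.165 |
| 6 | 0.056 | 0.064 | 0.084 | 0.118 |

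At ICC = 0 the simulation returns 0.048 to 0.051, as it should. A hand check uses the design effect DE = 1 + (31/t − 1)·ICC and P(F(2, 90) > 3.10 / DE). At ICC 0.05, DE is 2.50, 1.73 and 1.47 for t = 1, 2 and 3, giving 0.295, 0.172 and 0.127, close to the table.

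**5. Can the analysis alone repair it?** A test on therapist means holds its level, but at 31 per arm its power falls well below 0.80. As ICC goes from 0.01 to 0.10, power is 0.34 to 0.19 with two therapists per arm, 0.54 to 0.33 with three, 0.63 to 0.44 with four and 0.70 to 0.57 with six. With one per arm no such test exists, and more patients do not help, because therapist and arm are the same variable.

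**6. Therapists shared across arms.** If each therapist treats patients in all three arms and is a factor in the model, an additive therapist effect cancels from every arm contrast, and 93/117 stands.

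**The case against.** The best case for the plan is that the therapists are randomised and equally qualified, the conventional programme follows rehabilitation guidelines, the NMES cycle is fixed by the device, and patients, assessors and statisticians are blinded. These points reduce the likely size of a therapist effect and limit detection bias. They do not remove the nesting. Randomising a few therapists gives balance only on average over repeated trials, equal qualification is not equal effect, and blinded assessment does not equalise the care delivered.

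A second defence is that a therapist term is ordinary content for an analysis plan that is not shown. That is fair as to the model, and a missing term alone would not be a finding. But the allocation of therapists is fixed in this document. A later model cannot rescue one therapist per arm, and it costs much power with two or three.

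Some stronger readings are tempting, and the text does not support them:

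- A reader might infer that one person gives a patient all three components. The sentence speaks of therapists collectively and leaves this open.
- A reader might infer that those giving rehabilitation know the arm. Unblinding is stated for the rTMS operators only, and the Discussion attributes it to the visible menus.
- A reader might blame nesting for unblinded enthusiasm. Operators would be unblinded in a crossed design too, and the article already lists this as a limitation.
- A reader might call therapist and treatment fully confounded. That is true only with one therapist per arm. With several, it is a clustering problem.

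**Conclusion.** The point holds: the stated rule nests therapists in arms, while the stated test and sample size assume independent patients. The between-group test is therefore anti-conservative whenever therapists differ at all. How far depends on two figures that the document does not give. Across the assumed ranges the nominal 5% becomes about 10–50% with one therapist per arm, 7–30% with two, 7–22% with three and 6–12% with six. The mild end, about 6% with six therapists per arm and ICC 0.01, would matter little. The severe end would make a positive result uninterpretable. All treatment is given at one rehabilitation centre, so a small number per arm is plausible, but this is not documented. Confidence is high about the structure and only moderate about the size. The direction in which any particular arm would be favoured cannot be predicted.

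**What to change.** Replace the sentence that allocates therapists to groups with wording such as: *Available therapists of equivalent qualification will treat patients from all three arms. A patient's therapist will be set by timetable, independently of allocation, and therapist identity will be recorded.* At minimum, apply this to NMES and the conventional programme. Where existing staffing allows, have these two components given by someone who is not told the arm.

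Include therapist in the model for the primary outcome, at least as a sensitivity analysis. If nesting has to stay, state the number of therapists per arm and recompute the sample size with a justified ICC.

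Recruitment began on 1 September 2025, so some patients may already have been treated under the nested rule. Recover therapist identity for them, and report how many were treated before the change.

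The cost is rescheduling, a hand-over within the session where roles are split, one case report form field and one model term. The data will have a mixed nested and crossed structure. The rTMS operators stay unblinded, as the article acknowledges, and one who works across arms could still treat them differently.

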### Intervention methods

The intervention will be administered at the rehabilitation medical center of the Seventh People’s Hospital of Shanghai University of Traditional Chinese Medicine. All participants will receive the conventional rehabilitation program (CRP) recommended by the FS rehabilitation guidelines (37), which will include low-high grade joint mobilization, stretching exercise, passive and active limb movements, muscle strengthening, and self ROM exercises like different directions reaching, grasping and daily actions that are motivational and appropriate for the participants. Based on the CRP (30 min), control group C will receive Sham rTMS (20 min) + NMES (20 min); Intervention group A will receive LF-rTMS (20 min) + NMES (20 min); and Intervention group B will receive HF-rTMS (20 min) + NMES (20 min). The intervention for the three groups will be provided for 20 sessions (5 sessions per week, 4 weeks), each lasting 70 min.

### Neuromuscular electrical stimulation (NMES)

NMES (1–150 Hz and pulse width30-400 μs, the Chattanooga Wireless Pro 4, DJO FRANCE SAS) is specifically created for people requiring pain management and muscle strengthening, among other applications. The surface electrodes will be placed near the motor points of upper trapezius, supraspinatus, and deltoids (anterior, middle and posterior bundles) (Figure 2). Prior research indicated that eliciting contraction of the upper trapezius aids in stabilizing and elevating the scapula, thereby leading to external rotation of the scapula with the acromioclavicular joint serving as the pivot (38). The supraspinatus stabilizes the humerus within the glenoid fossa and coordinates the deltoids during shoulder abduction. The contraction of the anterior, middle and posterior deltoids facilitated the shoulder flexion, abduction and extension. Therefore, by moving the surface electrode (area = 2 × 2 cm^2^) on the skin above these target muscle bellies until a site is identified where minimum current elicits a visible muscle contraction without discomfort (39), typically in the range of tens of milliamps (between 20 mA and 50 mA). In stimulation therapy, the stimulator executed a cycle every 30 s, comprising 5 s for ramp-up, 10 s at peak stimulation, 5 s for ramp-down, and 10 s of no stimulation (40).

**Figure 2 fig2:**
[figure not shown]
NMES treatment for FS patients.

### Repetitive transcranial magnetic stimulation (rTMS)

The rTMS will use a Super-Rapid Magstim Stimulator (The Magstim Co., Whitland, UK) equipped with a figure-of-8 coil. As the two rings converge, the electric field peaks at its center (hot spot), stimulating a more accurately defined area (41). All the rTMS program will follow the International Federation of Clinical Neurophysiology guideline (42). A total of 20 rTMS sessions were performed over 4 weeks, with 5 sessions on 5 consecutive workdays and a 2-day maintenance break. Each rTMS session consisted of 30 trains of TMS pulses administered at 1HZ(LF-rTMS) or 10 Hz(HF-rTMS) for 10 s (100 pulses/train) with a 20s intertrain interval, resulting in 4,000 pulses per session for a total duration of 20 min (43). The target of the motor cortical region (M1) is at the contralateral hemisphere of the affected shoulder. The stimulation intensity will be set at 80% of the resting motor threshold, which is the minimum intensity that elicits an electromyographic response ≥50 μV in the first dorsal interosseous (FDI) of the hand contralateral to the stimulated hemisphere in at least 5 out of 10 trials. In this measurement, the figure-of-8 coil (Magventure) will be positioned over the upper limb motor hotspot and perpendicular to the central sulcus at a 45 °from the hemispheric midline (44) (Figure 3). The intensity for rTMS sessions will remain consistent throughout time and treatment arms.

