The maladaptive neuroplastic alterations are linked to FS, suggesting that treatment focused on reversing these changes is necessary (27). Repetitive transcranial magnetic stimulation (rTMS) is a non-invasive neuromodulation technique works by generating rapidly changing magnetic fields in specific regions of the cerebral cortex, which induce neuronal depolarization. This process can modulate neuronal excitability and synaptic plasticity in the underlying brain structures to restore cortical networks and may serve as suitable management alternatives for individuals with FS. The primary motor cortex (M1), located in the precentral gyrus of the frontal lobe is traditionally considered the brain region responsible for controlling voluntary movements of the contralateral limbs, however, recent studies have revealed that M1 also demonstrates neuroplasticity in relation to pain. The M1 neuronal projections to the periaqueductal gray (PAG) circuit encode information regarding sensory hypersensitivity associated with pain. M1 neurons can also project to tertiary neural circuits that include the mediodorsal thalamus and nucleus accumbent, recording the negative emotional dimensions of pain (28). The recent systematic review has also demonstrated that M1-rTMS can effectively reduce neuropathic pain (29), with M1 serving as the principal stimulation target for rTMS-induced analgesia. Multiple experimental studies have demonstrated that M1-rTMS possesses enhanced efficacy in reducing pain intensity, markedly diminishing the perceived severity of induced pain (30). The effects of rTMS at different frequencies on analgesia and cortical excitability differs: high-frequency (≥5 Hz) rTMS enhances cortical excitability, whereas low-frequency (≤1 Hz) rTMS diminishes cortical excitability. Both high and low frequencies may elicit analgesic effects (31). But the exact neural processes by which cortical plasticity contributes to FS remain unidentified.

If peripheral and cortical alterations are associated with FS, then rTMS and NMES training may be beneficial in treating this ailment for which effective treatment remains elusive. Therefore, the present protocol will be designed for a patient and assessor blinded, sham-controlled, randomized clinical trial, which will include 3 groups: Sham rTMS +NMES group (Group A), the LF-rTMS+NMES group (Group B) and the HF- rTMS+NMES group (Group C) and. The purposes of this protocol are as follows:

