Aim 1: To evaluate the efficacy of NMES combined with rTMS over the contralateral M1 area in reducing pain intensity and improving functional ability in patients with FS. And to compare the efficacy of LF-rTMS+NMES and HF-rTMS+NMES in patients with FS.

Aim 2: To investigate the correlation between the clinical efficacy and neuro-biomechanism of cortical alternation in patients with FS after conducting systematic evaluations both before and after treatment.

Aim 3: Based on this study protocol and its anticipated outcomes, clinicians can develop innovative management strategies for pain and motor function in patients with FS, aiming to achieve effective therapeutic results.

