### Sham-rTMS

In control group C, Sham rTMS will be delivered with the coil angle rotated 90° and only one wing of the coil touching the scalp of the participant to avoid inducing actual stimulation. The sound emitted during stimulation, the time and frequency of the sham rTMS will be the same as intervention group A and B (43).

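### One rTMS schedule is given for both active arms; its 4,000 pulses in 20 minutes cannot be delivered at 1 Hz, so the low-frequency dose is undefined

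*Protocol article*

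**What the plan says.** The section on repetitive transcranial magnetic stimulation describes one session pattern and applies it to both frequencies: "30 trains of TMS pulses administered at 1HZ(LF-rTMS) or 10 Hz(HF-rTMS) for 10 s (100 pulses/train"), with 20 s between trains, "resulting in 4,000 pulses per session for a total duration of 20 min". It gives no separate schedule for the LF arm, and neither does any other part of the article.

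The Intervention methods section repeats the 20-minute length for each active arm. For LF, which that section labels group A, it reads "Intervention group A will receive LF-rTMS (20 min) + NMES (20 min"), and HF has the same times. With 30 minutes of conventional rehabilitation, the sessions are "each lasting 70 min".

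Aim 1 in the Introduction includes the intention "to compare the efficacy of LF-rTMS+NMES and HF-rTMS+NMES in patients with FS". The Introduction also bases the choice of arms on frequency: "The effects of rTMS at different frequencies on analgesia and cortical excitability differs". The trial is under way: "Recruitment began on 1 September 2025".

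**The concern.** The sentence fixes the frequency, train length, pulses per train, number of trains, interval, total pulses and total time. These quantities are tied together by multiplication, so they can be checked, and they conflict. For HF the conflict looks like one wrong number. For LF it goes deeper, because 100 pulses cannot fit into 10 s at 1 Hz.

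The number of pulses is part of the dose. On its plain reading the sentence gives 4,000 pulses per session to both arms. A reader who accepts that would take an LF–HF difference as an effect of frequency at an equal pulse count, although a 20-minute session at 1 Hz cannot supply that count. The LF arm also could not be replicated from the published text. Operators working only from this specification would have to settle the conflict themselves and might settle it differently.

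**Working it through.** **Inputs.** From the rTMS section: 30 trains, 1 Hz or 10 Hz, 10 s per train, 100 pulses per train, 20 s interval, 4,000 pulses and 20 min per session, 20 sessions. From Intervention methods: 30 min rehabilitation + 20 min rTMS + 20 min NMES = 70 min.

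**Formulas.** Pulses = trains × frequency × train length. Duration = trains × (train length + interval).

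**HF, as written.**
- Pulses per train: 10 Hz × 10 s = 100, as stated.
- Total pulses: 30 × 100 = 3,000, against 4,000 stated.
- Duration: 30 × (10 + 20) s = 900 s = 15 min, against 20 min stated. Dropping the last interval gives 14.7 min.

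**HF with 40 trains.** 40 × 100 = 4,000 pulses, and 40 × 30 s = 1,200 s = 20 min. Both totals are met, and so is the 70-minute session.

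**LF.** Pulses per train: 1 Hz × 10 s = 10, against 100 stated. The possible readings are:

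| What is kept | Pulses per session | Stimulation time |
|---|---|---|
| 30 trains of 10 s | 30 × 10 = 300 | 15 min |
| 40 trains of 10 s | 40 × 10 = 400 | 20 min |
| 100 pulses per train (100 s each), 20 s interval, 20 min limit | 1,200 s ÷ 120 s = 10 trains; 10 × 100 = 1,000 | 20 min |
| Continuous 1 Hz, 20 min limit | 1 × 1,200 s = 1,200 | 20 min |
| 100 pulses per train, 30 trains | 3,000 | 30 × 120 s = 60 min |
| 100 pulses per train, 40 trains | 4,000 | 40 × 120 s = 80 min |
| 4,000 pulses without pauses | 4,000 | 4,000 s = 66.7 min |

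No row gives 4,000 pulses in 20 min. That combination needs an average rate of at least 4,000 ÷ 1,200 s = 3.33 Hz. Even without pauses, 4,000 pulses at 1 Hz would stretch the session to 30 + 66.7 + 20 = 116.7 min instead of 70.

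**Size within the 20-minute limit.** 300 to 1,200 pulses against 4,000 is 4,000 ÷ 1,200 = 3.3-fold to 4,000 ÷ 300 = 13.3-fold fewer. Over 20 sessions this is 6,000 to 24,000 against 80,000.

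**The case against.** The strongest reply is that the sentence may really be an HF schedule into which the 1 Hz option was inserted carelessly. Ten-second trains of 100 pulses, and 4,000 pulses in 20 minutes, all fit 10 Hz with 40 trains. The LF schedule would then be unstated rather than declared equal. The article nowhere claims dose equivalence; it equates session time and stimulation intensity. This is a plausible account of how the sentence arose, but the sentence still attaches its figures to both frequencies. If it is read as HF only, the article has no LF pulse schedule at all, and the HF figures still fail.

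A second reply is that a journal article condenses a fuller protocol, which may hold the correct LF settings. That would excuse an omission. It does not make contradictory printed figures right.

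Three points on the other side do stand:
- The 300-pulse floor uses the train count that is probably wrong. With 40 trains the floor is 400 pulses, or 10-fold fewer, so the 13.3-fold figure is the extreme of the range and the conclusion should not lean on it.
- Unequal pulse counts between frequencies at equal session time are not an error in themselves, and Aim 1 already names the arms as regimens.
- Nothing shows that any patient received inconsistent stimulation; a fixed and sensible LF program may be in use.

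The sham section's promise that "the time and frequency of the sham rTMS will be the same as intervention group A and B" is at most a side issue. If frequency there means pulse rate, one sham pattern cannot match both arms. It may instead mean the session schedule, and each patient hears only one pattern. The main conclusion does not depend on it.

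**Conclusion.** The point holds and should be corrected. The stated 4,000 pulses in 20 minutes are impossible at 1 Hz, where the ceiling is 1,200, or 30% of the stated count. The LF dose is therefore undefined, with readings from 300 to 1,200 pulses for a session of up to 20 minutes, or 400 to 1,200 if the train count should be 40. These are readings of the text, not delivered doses, which the article does not allow one to determine. The range assumes that the 20-minute limit is the figure to trust, which the 70-minute session supports.

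For HF, 30 trains in place of 40 is an inference, but a strong one, because 40 is the count that satisfies both totals. Alone it would be a minor slip. The weight of the finding lies with LF, as one of three arms and one side of a named comparison. Randomisation, the primary outcome and the planned analysis are not affected.

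**What to change.** - Print two schedules, one for LF and one for HF, each with trains, pulses per train, interval, total pulses and duration. Each should multiply out and agree with the settings actually delivered.
- For HF, change 30 trains to 40 if 40 is what is delivered.
- For LF, give the true pulse count; for example, continuous 1 Hz for 20 minutes is 1,200 pulses, if that is the program in use.
- State that session time, not pulse count, is equal between the active arms, and word any LF–HF conclusion as a comparison of two regimens rather than of frequency at equal dose.
- As a minor addition, say which pulse pattern the sham follows and that its sound is unmatched to the other arm.

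The cost is a text correction and a check of stimulator settings for patients treated since 1 September 2025. It needs no extra patients or staff and no change to allocation. Only if the LF settings have varied, or are changed now, would a dated amendment and a before/after flag in the dataset be needed.
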